## Abstract

**Background:**

Proximal humeral fractures are with an incidence of 4–5 % the third most common fractures in the elderly. In 20 % of humeral fractures there is an indication for surgical treatment according to the modified Neer-Criteria. A secondary varus dislocation of the head fragment and cutting-out are the most common complications of angle stable locking plates in AO11-A3 fractures of the elderly. One possibility to increase the stability of the screw-bone-interface is the cement augmentation of the screw tips. A second is the use of a multiplanar angle stablentramedullary nail that might provide better biomechanical properties after fixation of 2-part-fractures. A comparison of these two treatment options augmented locking plate versus multiplanar angle stable locking nail in 2-part surgical neck fractures of the proximal humerus has not been carried out up to now.

**Methods/Design:**

Forty patients (female/male, ≥60 years or female postmenopausal) with a 2-part-fracture of the proximal humerus (AO type 11-A3) will be randomized to either to augmented plate fixation group (PhilosAugment) or to multiplanar intramedullary nail group (MultiLoc). Outcome parameters are Disabilities of the Shoulder, Arm and Hand-Score (DASH) Constant Score (CS), American Shoulder and Elbow Score (ASES), Oxford Shoulder Score (OSS), Range of motion (ROM) and Short Form 36 (SF-36) after 3 weeks, 6 weeks, 3 months, 6 months, 12 and 24 months.

**Discussion:**

Because of the lack of clinical studies that compare cement augmented locking plates with multiplanar humeral nail systems after 2-part surgical neck fractures of the proximal humerus, the decision of surgical method currently depends only on surgeons preference. Because only a randomized clinical trial (RCT) can sufficiently answer the question if one treatment option provides advantages compared to the other method we are planning to perform a RCT.

**Trial registration:**

Clinical Trial (NCT02609906), November 18, 2015, registered retrospectively.

## Background

Proximal humeral fractures are with an incidence of 4–5 % the third most common fractures in the elderly [1]. These are the second most common upper-limb fracture after distal radial fractures [2, 3]. Sixty-five percent of all patients with a proximal humeral fracture are older than 60 years [1]. Being aware of the demographic change there will even be an increase of incidence of these fractures. Kannus et al. showed an incidence of 298 per 100,000 in the at least 80 years old patients in 2007 [4]. Palvanen et al. predict an increase of incidence of 50 % until 2030 [1].

Approximately 80 % of all humeral fractures are minimally or non-displaced and can be treated conservatively with a good functional result [5]. In 20 % of humeral fractures there is an indication for surgical treatment according to the modified Neer-Criteria [6]. These criteria are fulfilled if there is an angulation of at least 45 ° between fracture fragments, a displacement of the humeral shaft against the humeral head of at least 1 cm or a dislocation of the greater tuberosity of at least 5 mm [7]. Up to now there is no evidence for superiority of any surgical treatment in literature [8]. At the moment the most frequently used surgical technique for treatment of proximal humeral fractures is the angle stable plate fixation. There are various publications concerning this topic published by our research group [9, 10]. In our 10-years results a majority of patients showed excellent and good, but also 16 % showed unsatisfactory results after locking plate fixation [10]. Main risk for poor outcome was revision surgery caused by secondary displacement (14 %) which is also confirmed by results of other studies [11]. In a further study our research group could show that there is a higher risk for secondary displacement in 2-part-fractures with a gross primary dislocation or a large metaphyseal fracture zone (AO 11-A3), especially in osteoporotic patients [12]. Moreover these are common fractures and because of that a problem in surgical treatment.

A secondary varus dislocation of the head fragment and cutting-out are the most common complications of angle stable locking plates in AO 11-A3 fractures of the elderly. The primary reason for this mechanism of failure is certain instability of transmetaphyseal fractures in the region of the surgical neck caused by loss of impaction in a porous spongiosa. Because of that the forces on the head screws are high while the so called screw-bone-interface is rather weak after a surgical treatment.

Currently there exist various approaches to avoid a failure of the primary screw implantation. One possibility to increase the stability of the screw-bone-interface is the cement augmentation of the screw tips [13–18]. To date there exists no clinical study that reports the results of locking plate fixation and the augmentation of cannulated head screws although it is a widely used method in everyday surgery, especially in the elderly.

A second possibility to prevent secondary displacement after surgical treatment of 2-part-fractures is the use of an intramedullary nails [19–22]. A further development of intramedullary nails is multiplanar nailing. Screws can be inserted in various different levels and directions which can lead to a clearly higher stability [23–25].

A comparison of these two treatment options augmented locking plate versus multiplanar angle stable locking nail in 2-part surgical neck fractures of the proximal humerus has not been carried out up to now.

### Aim of the study

This randomized clinical study aims to compare cement augmented locking plate fixation versus a multiplanar humeral nail system for the treatment of displaced 2-part proximal humeral fractures in the elderly patient in terms of complication rate, shoulder function, quality of life and patient satisfaction.

### Hypothesis

We anticipate the cement augmented angle stable plate fixation system Philos™ with augmentation (Depuy-Synthes) achieves significant better outcome concerning intra- and postoperative complication and revision rate, functional outcome and patient satisfaction compared with the multiplanar proximal MultiLoc®-Nail (Depuy-Synthes).

## Methods/Design

### Study design

For comparative evaluation of the two treatment options: cement augmented plate fixation versus multiplanar intramedullary locking nail in proximal humeral fractures (AO Type 11-A3) we planned a single-centre parallel group, randomized controlled trial (RCT), following the CONSORT statement guidelines [26].

Forty patients will be randomized to either to augmented plate fixation group (PhilosAugment) or to multiplanar intramedullary nail group (MultiLoc). Patients will be recruited at our hospital (level I trauma centre). All subjects must provide written informed consent.

### Population, screening and randomization

The study will be conducted at the Department of Trauma Surgery, University of Munich (LMU), Germany. Patients will be screened within the regular emergency unit settings using the AO-Classification. Patients (female/male, ≥60 years or female postmenopausal) with a 2-part surgical neck fractures of the proximal humerus (AO type 11-A3). A correct fracture classification is ensured by CT-scans for all participants. Inclusion and exclusion criteria are listed in Table 1. Within 7 days, participants must be included. Inclusion and exclusion criteria are listed in Table 1. Within 7 days, participants must be included and randomized by sealed envelope (opaque, not resealable) drawing (Fig. 1). Each subject will have a unique identification number and keep that number throughout the study. Sequence generation was performed by online Statistical Computing Web Programme: www.randomization.com.

**Table 1 Tab1:** Inclusion- and exclusion criteria

Inclusion criteria	Exclusion criteria
• Age: ≥60 years, or female postmenopausal • 2-part fracture according to AO-classification (Arbeitsgemeinschaft für Osteosynthesefragen): AO 11-A3 • Signed informed consent • Patient can read and understand German	• Refusal to participate in the study • Not Independent • Dementia and/or institutionalized • Does not understand written and spoken guidance German • Pathologic fracture or a previous fracture of the same proximal humerus • Alcoholism or drug addiction, e.g., in the emergency department, breathalyzer indicates blood alcohol concentration of more than 2 % • Other injury to the same upper limb requiring surgery • Major nerve injury (e.g., complete radial- or axillary nerve palsy) • Rotator cuff tear arthropathy • Open fracture • Multi-trauma or -fractured patient • Fracture dislocation or head-splitting fracture • Non-displaced fracture • Isolated fracture of the major or minor tubercle • Any medical condition that excludes surgical treatment • Pregnancy

**Fig. 1 Fig1:**
[figure not shown]
Randomization and follow-up workflow

### Interventions

All fractures will initially be immobilised by a Gilchrist-bandage. This is the same procedure as for patients who do not attend this or any other trial and will be performed by the doctor on-duty in the emergency room. Patients will be admitted to the trauma ward after that. On the same day or at the latest on day after this patients will be informed about the current investigation, screened, included and randomized by one of the study investigators to our trial after written consent will be obtained as described above. The patients are allowed to make their decision within 24 h.

Operative treatment is exclusively performed by the below mentioned study investigators. The intervention group will be treated by the angle stable 3-hole plate fixation system Philos™ with augmentation (Depuy-Synthes) the comparison group by the multiplanar proximal humeral nail MultiLoc® with the length of 160 mm and a diameter according to the humeral shaft ((Depuy-Synthes). For plate fixation screws are set in a standardized fashion: Seven screws placed subcortical in row A, B, D and F as well as 3 screws bicortical in the shaft (one proximal non-locking and two distal locking screws). Whenever possible (according to contrast dye testing) the screws in row A and E are augmented with 0.5 ml Traumacem V+ (Depuy-Synthes). Alternatively screws in row B and D are used. The MultiLok nail is standardized fixed with three 4.5 mm MultiLoc screws at levels A, B and D. Two additional 3.5 mm screw-in-screws are used at levels A and B and aimed posteriorly. In the shaft one ascending calcar screw and two multiplanar distal locking screws are implanted. All study investigators are very experienced with both devices and have completed their learning curves.

### Types of outcomes and follow-up

The primary outcome will be the Disabilities of the Shoulder, Arm and Hand (DASH) Score after 24 months. The secondary outcome parameters are listed in Table 2 (Disabilities of the Shoulder, Arm and Hand-Score (DASH), Constant Score (CS), American Shoulder and Elbow Score (ASES), Oxford Shoulder Score (OSS), Range of motion (ROM) and Short Form 36 (SF-36) after 3 weeks, 6 weeks, 3 months, 6 months, 12 and 24 months. Further evaluation will be: Fracture reduction and healing results (radiographic findings), complications (Table 3) and revisions. Complications will be classified as described in Table 2. Follow-up examinations will take place after 3 weeks, 6 weeks, 3 months, 6 months, 12 and 24 months (Fig. 1). There will be no blinding of outcome assessment (Table 2).

**Table 2 Tab2:** Assessment and procedure of the trial

Assessment	Pre-operative	1. visit 6 weeks	2. visit 3 months	3. visit 6 months	4. visit 12 months	5. visit 24 months
Doctor’s visit	X	X	X	X	X	X
x-ray (true a.p., lateral, axial view)	X	X	X	X	X	X
CT-scan	X					
Inclusion criteria	X					
Consent	X					
Medical history	X					
ROM		X	X	X	X	X
CS			X	X	X	X
ASES		X	X	X	X	X
OSS		X	X	X	X	X
DASH		X	X	X	X	X
SF-36		X	X	X	X	X
Ultrasound for rotator cuff status					X	X

*ROM* range of motion, *CS* Constant Score, *ASES* American Shoulder and Elbow Score, *OSS* Oxford Shoulder Score, *DASH* Disabilities of the Shoulder, Arm and Hand, *SF-36* Score and Short Form 36

**Table 3 Tab3:** Complications

Classification of complications	
A) Implant associated complications/revisions	
A1) varus displacement	
A2) dorsal displacemenmt	
A3) varus and dorsal displacement	
A1-3) + S additional screw-cut-out	
A4) humeral shaft perforation	
A5) implant breaking	
A6) subacromial impingement	
A7) intraarticular cement malposition	
B) Non-implant associated complications/revisions	
B1) frozen shoulder	
B2) hematoma/seroma	
B3) infection	
B4) impairment of wound healing	
B5) nerve injury	
B6) avascular necrosis	
C) Technical complications/revisions	
C1) malposition of the implant	
C2) inadequate reduction	
D) Medical complications	
D1) venous thrombembolisms	
D2) pulmonary complications	
D3) cardiac complications	

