### Sample size estimation and statistical analysis

Primary outcome of our study is the DASH-Score (0–100 points, 0 (no disability) to 100 (most severe disability)) [27]. In a case number calculation for unpaired samples and target figures we assume an effect size of a difference of 15 points at the highest as there is a standard deviation of 15 points as well. A difference of 15 points is seen as a minimal clinically important difference. This data has been published in other studies before. It has been tested for plausibility and has been taken over after that. Following parameters are the results: Delta = 15, SD = 15, alpha = 0.05, power = 0.8. *N* = 40 patients will be included according to the above mentioned calculation. To protect the quality of our study the drop-out rate should not exceed 20 % (e.g. 3 patients per group).

Standard deviations or confidence intervals, in the case of percentages, will be provided for each type of epidemiological data. The assumption of normality will be verified by the Shapiro-Wilk test for the use of parametric tests. A Pearson’s chi-square test will be employed to analyse results from the two groups involving categorical variables. A Student’s (parametric) *t*-test will be used for comparing groups of numeric variables. Paired t-tests (parametric) and Wilcoxon tests (non-parametric) will be used to compare clinical progression at follow-up intervals. The significance level used in all statistical tests is to be 5 % (alpha = 0.05), with tests having a *P* value less than 0.05 being statistically significant.

Should differences be found in primary outcomes, then statistical methods will be used to test whether there is robust correlation between epidemiological factors or fracture seriousness and the observed functional outcomes. In addition, we intend to employ Kaplan-Meier survival analysis to evaluate drop-outs should high rates of complications (greater than 20 %) occur in either assignment group.

Patients who experience treatment failures and require additional surgery will be monitored and their results computed in the primary assignment group (intention-to-treat principle). Provisions are to be made for blinded statistical analysis of data by a statistician who is unfamiliar with the objectives and outcomes of interest.

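### No pre-injury DASH or SF-36 is collected, so the 24-month comparison gives up some precision, and a chance imbalance in prior arm function could be neither seen nor adjusted for

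*Protocol article*

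**What the plan says.** In the protocol article, Types of outcomes and follow-up, the primary endpoint is one post-operative value: "The primary outcome will be the Disabilities of the Shoulder, Arm and Hand (DASH) Score after 24 months". The same section adds: "Follow-up examinations will take place after 3 weeks, 6 weeks, 3 months, 6 months, 12 and 24 months (Fig. 1". Table 2 gives the schedule by instrument. Its pre-operative column marks the doctor's visit, x-ray, CT, inclusion criteria, consent and history ("Medical history X"). It is empty for DASH, SF-36, ASES, OSS, Constant Score and range of motion. No recalled pre-injury score is mentioned anywhere in the article.

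Table 1 (Population, screening and randomization) admits patients by "Age: ≥60 years, or female postmenopausal". Exclusions that bear on prior function include "Not Independent", dementia or institutional care, "Rotator cuff tear arthropathy", "Pathologic fracture or a previous fracture of the same proximal humerus", major nerve injury, and a further injury of the same limb that needs an operation. No criterion limits other prior disability of the arm.

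On analysis (Sample size estimation and statistical analysis): "A Student’s (parametric) *t*-test will be used for comparing groups of numeric variables". No baseline covariate is named. Epidemiological factors and fracture severity are to be examined only if a difference in the primary outcome has been found.

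**The concern.** The DASH scores the whole upper limb on an absolute 0 to 100 scale. A patient with, say, hand osteoarthritis or a cuff tear without arthropathy is eligible and may carry DASH points that predate the fracture. These conditions are illustrations; the article does not say how common they are.

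With about 20 patients per arm, such points can fall unevenly by chance. Without a pre-injury score, the investigators could not see this, and no later analysis plan could adjust for it. The conditional look at epidemiological factors does not help, because an imbalance that masks a difference would never trigger it. At stake is how precise and how interpretable the primary comparison is in a small trial.

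**Working it through.** **Inputs.** From Sample size estimation and statistical analysis: difference 15, SD 15, alpha 0.05 (two-sided assumed), power 0.8, N = 40, dropout example of 3 per group. Allocation is taken as 1:1, so 20 per arm, or 20 − 3 = 17 per arm after dropout. Assumed, not in the document: correlation r between pre-injury and 24-month DASH of 0.3 to 0.5.

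**1. The plan's own figure.** n per arm = 2 × (1.960 + 0.842)² × 15²/15² = 15.7, so 16; the exact t-test needs 17 (power 0.807). With dropout, 16/(1 − 0.20) = 20, or 17 + 3 = 20 per arm, which gives 40. The stated N reproduces, and the missing baseline does not change it.

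**2. Validity of the unadjusted test.** In 40,000 simulated trials per setting (20 per arm, no treatment effect, outcome SD 15), the type I error was 5.1 % (r = 0.3), 4.8 % (r = 0.5) and 5.0 % (r = 0.7). The mean difference stayed within 0.03 points of zero. The test is valid.

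**3. Precision forgone.** Residual SD = 15 × √(1 − r²). Half-width = t × residual SD × √(2/n), with t on 38 degrees of freedom (n = 20) or 32 (n = 17).

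| r | Residual SD | Half-width, 20 per arm | Half-width, 17 per arm | Power, 17 per arm |
|---|---|---|---|---|
| 0 (unadjusted) | 15.0 | 9.6 | 10.5 | 81 % |
| 0.3 | 14.3 | 9.2 | 10.0 | 84 % |
| 0.5 | 13.0 | 8.3 | 9.1 | 90 % |

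Expressed as sample size, 20/(1 − r²) = 22.0 (r = 0.3) or 26.7 (r = 0.5) per arm. The approximation ignores the one degree of freedom spent on the covariate and the estimation of its slope, so the gains are slightly flattering.

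**4. How far a chance imbalance could move the result.** If the pre-injury SD is b, the imbalance has standard error b × √(2/n), and the slope onto the outcome is r × 15/b. The product is r × 15 × √(2/n), so b cancels.

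- 20 per arm: standard error of the shift 1.42 (r = 0.3) or 2.37 (r = 0.5). In 95 % of trials the shift is at most 1.96 times this, 2.8 or 4.65 points. The chance of a shift above 5 points is 0.04 % or 3.5 %.
- 17 per arm: 95 % limits 3.0 or 5.0 points; chance of a shift above 5 points 0.1 % or 5.2 %.

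The planning difference is 15 points.

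**The case against.** **Randomisation already deals with prior disability.** This stands for bias and type I error. Prior function is equal between arms in expectation, and its spread between patients is part of the t-test's standard error, provided the planning SD of 15 includes it. A reader might infer that prior disability is confounded with the implant effect; a randomised design and step 2 do not support that.

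**The imbalance sounds larger than it is.** Also right. With an assumed pre-injury SD of 10 to 15, the chance that the arms differ by more than 5 points before injury is 11 % to 29 %, and it is tempting to set that against the target of 15. But that is an imbalance in the covariate, and only the fraction r × 15/b reaches the outcome. Step 4 gives the relevant figures.

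**Table 1 already removes the worst cases.** Partly. It excludes dependent patients and several major conditions of the shoulder and limb, but nothing in it limits milder or more distal arm disability.

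**Return to pre-injury level is not an aim.** Correct. Aim of the study is to compare two implants, so the inability to report recovery to a prior level is no defect against it.

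**Covariate adjustment belongs in an analysis plan.** True of the choice of model. But an analysis plan cannot adjust for a score that was never collected, and Table 2 is an explicit schedule. The history taken before surgery is not described as including any functional score.

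**Conclusion.** The point holds as a cheap improvement, not as an error that invalidates the trial. The primary comparison is unbiased, the type I error is kept and N = 40 stands. What is lost is precision: 0.4 to 1.3 points of half-width at 20 per arm (9.6 − 9.2 and 9.6 − 8.3), or 3 to 9 percentage points of power at 17 per arm. So is any means of seeing or correcting a chance imbalance in prior function. These sizes rest on the assumed r of 0.3 to 0.5 and on the plan's SD of 15. At the lower end of the range the gain is small.

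**What to change.** Add DASH and SF-36, recalled for the week before the injury, to the pre-operative column of Table 2. They should be completed after consent and before the envelope is opened. A score describing the arm after the fracture would measure the injury, so recall is the workable form. Replace the unadjusted t-test for 24-month DASH with ANCOVA on arm and pre-injury DASH.

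For patients already enrolled, use a missing-value indicator for the covariate. Late recall would follow surgery in a trial without blinded outcome assessment and could be coloured by the implant or the result.

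Cost: a short added questionnaire session at the contact described under Interventions, where an investigator already informs, consents and randomises the patient, with no extra visit or staff. Recall error remains; it weakens the covariate, but it cannot depend on arm when collected before randomisation.

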### Sample size estimation and statistical analysis

Primary outcome of our study is the DASH-Score (0–100 points, 0 (no disability) to 100 (most severe disability)) [27]. In a case number calculation for unpaired samples and target figures we assume an effect size of a difference of 15 points at the highest as there is a standard deviation of 15 points as well. A difference of 15 points is seen as a minimal clinically important difference. This data has been published in other studies before. It has been tested for plausibility and has been taken over after that. Following parameters are the results: Delta = 15, SD = 15, alpha = 0.05, power = 0.8. *N* = 40 patients will be included according to the above mentioned calculation. To protect the quality of our study the drop-out rate should not exceed 20 % (e.g. 3 patients per group).

Standard deviations or confidence intervals, in the case of percentages, will be provided for each type of epidemiological data. The assumption of normality will be verified by the Shapiro-Wilk test for the use of parametric tests. A Pearson’s chi-square test will be employed to analyse results from the two groups involving categorical variables. A Student’s (parametric) *t*-test will be used for comparing groups of numeric variables. Paired t-tests (parametric) and Wilcoxon tests (non-parametric) will be used to compare clinical progression at follow-up intervals. The significance level used in all statistical tests is to be 5 % (alpha = 0.05), with tests having a *P* value less than 0.05 being statistically significant.

Should differences be found in primary outcomes, then statistical methods will be used to test whether there is robust correlation between epidemiological factors or fracture seriousness and the observed functional outcomes. In addition, we intend to employ Kaplan-Meier survival analysis to evaluate drop-outs should high rates of complications (greater than 20 %) occur in either assignment group.

Patients who experience treatment failures and require additional surgery will be monitored and their results computed in the primary assignment group (intention-to-treat principle). Provisions are to be made for blinded statistical analysis of data by a statistician who is unfamiliar with the objectives and outcomes of interest.

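### Kaplan-Meier is aimed at drop-outs but switched on by complications, and the factor analysis runs only if the arms differ: both should run whatever the results, with the survival method applied to complications and revisions

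*Protocol article*

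**What the plan says.** Two follow-on analyses appear in the protocol article under Sample size estimation and statistical analysis.

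- **Survival analysis.** Target and condition stand in one sentence: "Kaplan-Meier survival analysis to evaluate drop-outs should high rates of complications". The target is drop-out. The condition is complications, with the limit given as "should high rates of complications (greater than 20 %) occur in either assignment group".
- **Factor analysis.** The condition is a difference in the primary outcome: "Should differences be found in primary outcomes, then statistical methods will be used to test". The target is a "robust correlation between epidemiological factors or fracture seriousness and the observed functional outcomes". What counts as a difference is not defined.

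Three other statements bear on these:

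- The Hypothesis section expects the augmented plate to show "significant better outcome concerning intra- and postoperative complication and revision rate", and the Aim of the study section also names the complication rate.
- Types of outcomes and follow-up lists "complications (Table 3) and revisions" as a further evaluation, with no condition attached.
- The last paragraph of the statistical section keeps patients with treatment failure and further surgery under observation and counts them in their assigned arm. Earlier in that section, the drop-out rate has its own ceiling of 20 %, with 3 patients per group as the example.

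**The concern.** **Survival analysis.** Loss to follow-up is normally what censors a survival curve; the event of interest is the complication or revision. Here a high complication rate would produce a curve of drop-outs. An arm that lost many patients but had few complications would produce none. In neither case does the method describe when fixations fail, although failure of fixation is the clinical problem that motivates the trial.

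**Factor analysis.** The relation between age, sex or fracture severity and DASH does not depend on whether the arms differ. In a 40-patient trial with no stratification described, chance imbalance can mask a difference as well as create one, yet only a positive result is examined further. A correlation between a factor and the outcome also does not estimate the arm difference with that factor held fixed.

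At stake is whether positive and null trials get the same analyses, and whether the timing of complications and revisions is analysed at all. The validity of the primary test is not at stake.

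**Working it through.** **1. Sample size, to fix the number per arm.** Inputs from the statistical section: difference 15, SD 15, alpha 0.05 (two-sided assumed), power 0.80. The normal formula gives n = 2 × (1.96 + 0.84)² × (15/15)² ≈ 15.7, so 16 per arm; 16 / (1 − 0.20) = 20 per arm, 40 in total. With the t-distribution 17 per arm are needed (power 80.7 %), and 17 + 3 drop-outs = 20 per arm. Both routes reproduce N = 40. The allocation ratio is not stated; 1:1 is assumed.

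**2. Is a complication a drop-out in this protocol?**

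| Item | What the protocol does with it |
|---|---|
| Treatment failure with further surgery | Patient followed on, counted in the assigned arm |
| Drop-out | Patient lost; own ceiling of 20 % (example 3 of 20 = 15 %) |
| Trigger for Kaplan-Meier | Complications above 20 % in either arm |
| Target of Kaplan-Meier | Drop-outs |

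The first two rows separate the concepts; the last two join them. The drop-out ceiling triggers nothing.

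**3. How often would the Kaplan-Meier trigger fire?** More than 20 % of 20 patients means at least 5. With q = P(X ≥ 5) for X ~ Binomial(20, p), and the same true rate p in both arms, P(either arm crosses) = 1 − (1 − q)².

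| True rate p | q | Either arm |
|---|---|---|
| 10 % | 0.043 | 8 % |
| 14 % | 0.137 | 26 % |
| 20 % | 0.370 | 60 % |
| 25 % | 0.585 | 83 % |
| 30 % | 0.762 | 94 % |

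The 14 % is the Background section's figure for revision surgery caused by secondary displacement. It is not an overall complication rate, and Table 3 counts many more event types. The table is therefore a range and not a forecast.

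**4. How often would the factor analysis be run?** Assume that a difference means p < 0.05 in the t-test, with 17 to 20 evaluable per arm and SD 15. From the noncentral t-distribution:

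| True DASH difference | Run | Skipped |
|---|---|---|
| 0 | 5 % | 95 % |
| 7.5 | 29–34 % | 66–71 % |
| 10 | 47–54 % | 46–53 % |
| 15 (planned) | 81–87 % | 13–19 % |

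**5. What would routine adjustment for age and sex do to power?** With 17 per arm, the standardised difference becomes 1/√(1 − R²), where R² is the share of DASH variance explained, and the error degrees of freedom fall from 32 to 30.

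| R² (assumed) | Power |
|---|---|
| Unadjusted | 80.7 % |
| 0 | 80.5 % |
| 0.1 | 84.5 % |
| 0.2 | 88.4 % |

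The documents give no R², so a gain cannot be claimed, only bounded under assumptions. If the covariates explain nothing, the loss is about 0.2 percentage points.

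**The case against.** The strongest reply is that the complication aim already has an analysis. The aim and hypothesis speak of rates, complications and revisions are evaluated unconditionally, and the same statistical section plans a chi-square test for categorical variables between groups. The protocol never promises a time-to-event analysis. This stands: a reader might infer that complications go unanalysed at or below 20 %, and the documents do not support that. What is lost is timing and the handling of incomplete follow-up.

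Nor does it follow that drop-outs go unexamined. The protocol follows CONSORT and sets a drop-out ceiling, so losses must be counted. Only the survival analysis of them is conditional.

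On the factor analysis, the correlation is a legitimate exploratory question and is not presented as adjustment. The unadjusted t-test on randomised arms is valid at any sample size, and the choice of covariates is commonly left to an analysis plan. This also stands, so calling the correlation the wrong quantity would go too far. It does not rescue the gate, which the article states outright.

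It can also be said that an overall complication rate of 25 % or more would make the Kaplan-Meier trigger fire in most trials. That is true, but it would then deliver a curve of drop-outs. Reading drop-outs as loose wording for implant failure would resolve the mismatch, but the intention-to-treat sentence and the separate drop-out ceiling speak against that reading.

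**Conclusion.** The point holds in a limited form. The mismatch between trigger and target is explicit in the text: complications switch on an analysis of drop-outs, although the protocol treats the two as different things. The survival method therefore misses the complication and revision outcomes in the aim and hypothesis, and whether it is run varies from about 8 % to 94 % of trials as the common true rate goes from 10 % to 30 %. The factor analysis is gated on the primary result and would be skipped in roughly half of trials with a true 10-point difference.

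The figures assume 1:1 allocation, complications counted over 20 patients per arm, the same true rate in both arms, two-sided alpha and, for the factor analysis, that a difference means p < 0.05.

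The severity is moderate. The DASH t-test, N = 40 and the chi-square comparison of complication and revision proportions are unaffected. The change is still worth making, because it gives positive and null results the same analyses and adds timing to a stated aim.

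**What to change.** Replace the two conditional sentences with three commitments:

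1. Report time to first complication and time to first revision by arm, whatever the observed rate. Use cumulative incidence (Aalen-Johansen) with death as a competing event, or Kaplan-Meier with death censored. The choice must be stated, because a Kaplan-Meier curve does not treat death as a competing event. Tabulate drop-outs separately by arm, visit and reason.
2. Report the 24-month DASH difference adjusted for age and sex as a pre-specified supportive analysis, whether or not the unadjusted t-test is significant. The t-test stays primary.
3. If the factor-outcome correlations are wanted, keep them, run them unconditionally and label them exploratory.

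The cost is a few sentences and minor programming. No extra patients or visits are needed; the adjustment uses two degrees of freedom. Complication, revision and death dates need to be recorded so that event times can be computed.
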